**Fig. 1 Fig1:**
[figure not shown]
Important risk factors for awareness with paralysis include sedation under dosing, neuromuscular blocker use, and a lack of protocolled monitoring of sedation depth. Every major risk factor for awareness with paralysis commonly occurs in the emergency department

The data cited above provided our research group with the preliminary data to justify further study of AWP among mechanically ventilated ED patients. The ED-AWARENESS Study was a single-center, prospective cohort study which consecutively enrolled 383 mechanically ventilated ED patients over a 12-month period at a large academic medical center [19, 20]. Among survivors given NMB in the ED, the proportion of patients experiencing AWP was 3.3% (10/306; 95% CI, 1.6–5.9%) [19]. In an a priori secondary analysis of the multicenter ED-SED Pilot Trial, we demonstrated that 4.1% (13/314; 95% CI, 2.2–7.0%) of survivors that were given a NMB in the ED experienced AWP [21–23]. Finally, in a single-center prospective cohort conducted at Hennepin County Medical Center (an enrolling site for the current trial), the proportion of patients experiencing an AWP event was 7.4% (66/886; 95% CI, 5.8–9.4%) [24]. Taken as a whole, these data justify a clinical trial aimed at prevention of AWP among mechanically ventilated ED patients and strongly suggest the ED could be a high-yield arena in which to improve patient-centered clinical outcomes.

Psychological trauma and PTSD are a significant burden among the critically ill. PTSD is the development of significant distress or social impairment in someone directly or indirectly exposed to death, threated death, injury, or violence. Critical illness is psychologically traumatic, and 25–35% of survivors experience PTSD [25–27]. These survivors have worse quality of life, greater frequency of pain and substance abuse, increased healthcare cost, and threefold greater risk of death [28–33].

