### Interventions

Patients in the control phase of the trial will receive usual, clinician-directed care. To limit a Hawthorne-like effect, clinicians will have no knowledge of the study during the control. After 6 months, as determined by computer-generated randomization, a site will enter a 2-month transition phase, during which we will implement a multifaceted intervention aimed at reducing the use of rocuronium in the ED and consequently increase the use of succinylcholine. The intervention will be delivered at the cluster level, and the strategies employed revolve around the use of “nudges” without restricting clinician choice [50]. Nudges can be a powerful strategy to modify clinician behavior in order to increase uptake of evidence-based practices [48, 50–52]. A type of nudge involves the use of “defaults”; default options are those set in place when no alternatives are actively chosen and they have been shown to positively influence clinician decisions [50]. Succinylcholine will be the default NMB over rocuronium because (1) it has been the default NMB of choice in the ED for > 40 years [53]; (2) its 5-min duration of action greatly reduces AWP risk; (3) our preliminary data regarding AWP and its association with rocuronium [19, 23]; (4) ED rocuronium use has increased despite no patient-centered studies showing benefit over succinylcholine [17, 21]; and (5) a robust body of literature which documents equivalent efficacy and safety profiles of succinylcholine and rocuronium [54–56].

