A basic challenge of pragmatic clinical trials is to design an intervention that is appropriately balanced with respect to flexibility (i.e., it must be adaptable to local culture) and adherence (i.e., it must cause some level of change in order for efficacy to be adequately tested). In addition, a fundamental aspect of nudges is their influence on decisions without restricting choice. Due to these issues, our multifaceted intervention strategy will have both mandatory (standardized) and optional interventions during the transition phase. For the mandatory interventions, we will educate and engage (1) with emergency medicine (EM) physician and nursing leadership to secure endorsement of the trial; and (2) to deliver standardized presentations and lectures to clinicians and trainees (e.g., grand rounds, faculty meetings). We will also use passive alerts in the form of (1) strategically placed laminated graphics which advertise and promote the trial in the ED; and (2) distribution of a one-page document, which contains the background, rationale, and goals of the trial in one convenient location. Finally, active alerts will include (1) announcement of succinylcholine as the default NMB in the nursing “huddle” (before shifts); and (2) monthly emails to clinicians showing the breakdown of NMB use (continuous quality improvement). Optional interventions will be dictated by local culture and resources, or as needed if intervention fidelity declines over time. These include the use of ED-based pharmacy resources to advertise and promote the trial, as well as modification of access to rocuronium, making succinylcholine a more “convenient” option to clinicians (e.g., in the bedside airway box versus the automated medication dispensing system). If needed, we will identify more local champions, in addition to each site principal investigator, to participate in and promote the trial. Finally, if needed we will send emails to individual clinicians each time rocuronium is used in order to explore the rationale for its choice. This provides *accountable justification* regarding NMB choice (i.e., justification of the decision to not use the default). After the 2-month transition phase, each site will begin the intervention phase, in which enrollment will be resumed.

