### Data

Patient-level data will be easily accessible from the electronic medical record. The following baseline characteristics will be collected: age, gender, race, weight, height, pre-existing comorbid conditions, vital signs at presentation, and pertinent laboratory variables. Pre-intubation mental status, drugs used to facilitate intubation, and ventilator settings in the ED will be collected. After the initiation of mechanical ventilation in the ED, all medications related to analgesia and sedation in the ED will be collected. Sedation depth in the ED will be recorded by bedside nurses, using validated sedation depth scales, such as RASS or the sedation-agitation scale (SAS), per existing protocols [70].

The following in-hospital data will be collected: duration of ventilation, agents used for analgesia and sedation during the first 24 h of ICU admission, depth of sedation during the first 7 days after admission, lengths of stay in the ICU and hospital, discharge location, and mortality status (Table 1).

**Table 1 Tab1:** Schedule of screening, data collection, and outcomes assessments for the ED-AWARENESS-2 Trial

Measurement/event	ED	Extubation	^a^1	2	3	4	5	6	7	MV^b^	HOSP D/C	Day 30	Day 180
Inclusion criteria	X												
Exclusion criteria		X											
Demographics, baseline data	X												
Laboratory values	X												
Blood gas values	X		X										
ED procedures and care	X												
Intubation meds and location	X												
Safety events (i.e., intubation success, unplanned extubation, cardiac arrhythmia, allergy, MH)	X												
Ventilator settings/data	X												
Sedation depth (RASS, SAS), documented by bedside nurse	X		X	X	X	X	X	X	X				
Medications for sedation, analgesia, NMB	X		X										
Delirium assessment/CAM-ICU			X	X	X	X	X	X	X				
Assessment of AWP		X											
Ventilator duration										X	X		
Length of stay (hospital and ICU)											X		
Discharge location											X		
Mortality status											X		
Mental health and QOL assessments												X	X

*ED* emergency department; *MV* mechanical ventilation; *MH* malignant hyperthermia; *RASS* Richmond Agitation-Sedation Scale; *SAS* Sedation-Agitation Scale; *NMB* neuromuscular blockade; *CAM* confusion assessment method; *ICU* intensive care unit; *QOL* quality of life

^a^The numbers 1–7 refer to hospital days, with hospital day 1 referring to the first day after admission from the ED

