Instrumental variable (IV) methods will be used to account for non-adherence, as there could be differences between intervention effectiveness (i.e., effect among all patients to whom the intervention is targeted) and efficacy (i.e., effects among patients whose clinicians adhere to the intervention). We will use a non-parametric IV estimator adapted to stepped wedge designs, and IV regression methods to estimate complier average causal effect (CACE) of the intervention [79]. To avoid conflating the effect of time with the intervention effect, we will (1) obtain step-specific CACE estimates and (2) summarize step-specific estimates across all steps. We will also use two-stage residual inclusion to perform IV regression, using individual data from all six time points, adjusting for time and cluster effects [80–82]. Unlike per-protocol analyses, CACE analyses are not biased by selection effects and have been shown to be valid inferential approaches in stepped wedge trials [79].

We will determine proportion (with 95% CIs) of patients with clinically significant PTSD symptoms (PCL-5 score > 32) at 30 days and 180 days post-discharge [83, 84] and compare the control versus the intervention phase. To test the independent association of AWP (main exposure of interest) with 30-day PTSD symptom development, multivariable logistic regression will be used, with covariates selected for inclusion a priori [85]. The model will be adjusted for covariates previously associated with PTSD symptoms in critical illness survivors: (1) age; (2) sex; (3) prior psychological trauma (PC-PTSD-5 score)/mental health history; (4) illness severity; and (5) receipt and dose of benzodiazepines [10, 25, 26, 62, 86, 87]. We will adjust for race, given known racial disparities in PTSD symptoms [88–91]. To examine time trends in PTSD symptoms, and independent effects of AWP on time trends, mixed effect logistic regression will be used. Individual random intercept and random time slope will be specified and tested along with other potential risk factors. We will identify individual-level potential risk factors which could explain variation in individual time trend by testing interaction between random time slope and risk factor(s). In all of these models, cluster effect will be modeled as a fixed effect, using cluster indicator in the model. Similar analyses will be conducted for the other secondary outcomes.

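### The protocol calls the secondary CACE analysis valid without stating its no-other-path condition, and the step-specific CACE cannot be adjusted for site

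*Protocol article*

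**What the plan says.** Proposed statistical methods plans a "non-parametric IV estimator adapted to stepped wedge designs, and IV regression methods to estimate complier average causal effect (CACE) of the intervention". Trial phase is the instrument. Efficacy is described as "effects among patients whose clinicians adhere to the intervention"; the article does not define treatment received further, and I take it to be the blocker chosen.

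Two forms are planned. The first is to "obtain step-specific CACE estimates" and then summarise them across steps; the reason given is to keep the time effect apart from the intervention effect, and no site term is mentioned. The second is two-stage residual inclusion on individual data from all periods, with terms for time and cluster. The paragraph closes with the statement that "CACE analyses are not biased by selection effects and have been shown to be valid inferential approaches" in stepped wedge trials.

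Other sections bear on this:

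- Interventions: the mandatory package is meant, among other things, "to deliver standardized presentations and lectures to clinicians and trainees". It also includes posters, a one-page rationale, announcements before shifts and monthly emails.
- Interventions, on usual care: "clinicians will have no knowledge of the study during the control".
- Fig. 1 legend: "Important risk factors for awareness with paralysis include sedation under dosing", and it also lists blocker use and lack of protocolised sedation monitoring.
- Data: "all medications related to analgesia and sedation in the ED will be collected", and sedation depth is recorded.
- Trial design: one site crosses at each step, from the second to the sixth period.
- Proposed statistical methods, primary model: site is a fixed effect because there are only five clusters.

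**The concern.** An instrumental-variable estimate divides the whole phase effect on AWP by the phase effect on treatment received. It therefore needs an exclusion condition: phase must not act on AWP by any other route. In particular, intervention-phase patients who still receive rocuronium must be unaffected by the phase. The closing sentence speaks only to selection and does not mention this condition.

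The design gives reason to doubt the condition. Phase switches on the default agent and the education about AWP together, and neither is present in the control phase. If clinicians who have been taught about AWP also sedate earlier or more fully, that benefit enters the numerator and is attributed to adherence.

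The step-specific form raises a second, separate matter. Within one period some sites are in intervention and the rest in control, so phase is a function of site. A site effect cannot be estimated there, although the primary model relies on site effects.

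At stake is what the trial may conclude about blocker choice as distinct from the intervention as a whole.

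**Working it through.** **The plan's own figure.** The article states no number for the CACE. Its sample size is 3090 = 5 sites × 6 periods × 103. With a Hussey-Hughes variance, ICC 0.001, 3.3% versus 0.6% and two-sided α 0.05, 103 per cell gives 80.4% power when the control-rate binomial variance is used (about 95.5% with the average of the two variances). So 3090 is reproducible. It is not in dispute, and only the equal cell size is used below.

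**A. A second path from phase to AWP**

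Inputs:
- Planned effect: 3.3 − 0.6 = 2.7 points (Sample size justification).
- Earlier rocuronium use: 49% and 60% (Background), which limits how far it can fall. The expected fall π is not stated; I assume 0.3 to 0.5.
- Non-drug effect δ on AWP across all patients: not stated; I use 0.5 point as an illustration.

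Formula: CACE = (agent path + δ)/π, so the shift due to δ is δ/π.

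| π | 0.5/π (points) |
|---|---|
| 0.5 | 1.00 |
| 0.4 | 1.25 |
| 0.3 | 1.67 |

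On the planned effect: at π = 0.5 the CACE reads 2.7/0.5 = 5.4 points. If a quarter of the 2.7 points came by a non-drug route, the part due to the agent would be 0.75 × 2.7/0.5 = 4.05 points.

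Adjusting for site and period does not remove this shift. It applies equally to the two-stage regression.

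**B. Site and phase within a step**

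Period 1 is all control and period 6 all intervention, so only periods 2 to 5 give a within-period contrast (1 v 4, 2 v 3, 3 v 2 and 4 v 1 sites).

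Inputs: one enrolling site had an earlier AWP rate of 7.4% (Background). The other four are set at 3.3%, which is an assumption; 3.3% is the protocol's planning rate. There is no true effect, and cells are equal.

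If the 7.4% site crosses first, the intervention-minus-control contrasts are:
- Period 2: 7.4 − 3.3 = 4.10
- Period 3: (7.4 + 3.3)/2 − 3.3 = 2.05
- Period 4: (7.4 + 2 × 3.3)/3 − 3.3 = 1.37
- Period 5: (7.4 + 3 × 3.3)/4 − 3.3 = 1.03 (1.025 before rounding)

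The equal-weight mean is 2.14. With weights proportional to n₁n₀/(n₁+n₀), that is 4, 6, 6, 4, the mean is 41.0/20 = 2.05.

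Weighted mean by crossing position of that site:

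| 1st | 2nd | 3rd | 4th | 5th |
|---|---|---|---|---|
| +2.05 | +1.03 | 0 | −1.03 | −2.05 |

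Over all 120 orders the mean is 0 and the SD 1.45 points. Division by π = 0.5 turns ±2.05 into a spurious CACE of ±4.1 points. I hold π fixed; the denominator is open to the same aliasing, which I have not quantified.

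**How this compares with the protocol's ICC.** The scenario has a between-site SD of √(4.1² × 0.8/4) = 1.83 points around a mean of 4.12%. That is an ICC of 0.000336/(0.0412 × 0.9588) = 0.0085. At the protocol's 0.001 the site SD is √(0.001 × 0.033 × 0.967) = 0.00565, or 0.565 point. The SD over orders scales with it: 1.45 × 0.565/1.83 ≈ 0.45 point.

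**The case against.** The case against is substantial, and much of it stands.

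- **The documents do not show that sedation will change.** The listed education concerns the trial and the default agent; no teaching on sedation practice is described. Background reports no association of AWP with sedation variables in preliminary data. This stands, so the point is conditional. But that evidence rests on 23 AWP cases, and the same section cites another cohort in which rocuronium was not associated with AWP. Attribution to the agent is thus an open question.
- **The plan speaks of the CACE of the intervention, not of the drug alone.** True, but an estimate among adherers still assumes that phase does nothing for non-adherers.
- **A sedation change could come from the agent.** Background says paralysed patients get less sedation, and later. A shorter-acting agent could alter that, and such a path does not violate the condition. This stands and limits the remedy: a model of sedation by phase cannot separate the two routes, so a sedation effect should not simply be subtracted.
- **A site-adjusted CACE is already planned, and site imbalance averages to zero over randomisation.** Both true. What remains is which form leads, and that only one order is realised.

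Three stronger readings are tempting. A reader might infer that the step-specific intervals are too narrow. The article gives no variance method, which may sit in the SAP, and cluster-level or permutation inference would avoid the problem. A reader might also divide the planned effect by an assumed fall in rocuronium use and find the result implausible beside earlier AWP risks. That would question the planning effect, not the instrumental-variable method. Finally, a reader might extend the criticism to the primary result. The primary intention-to-treat model has fixed site effects and does not use the instrument.

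**Conclusion.** The point holds in a limited form, for a secondary analysis.

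First, the validity sentence claims more than its reason supports. The no-other-path condition is neither stated nor safe, given what the phase delivers and what the protocol itself lists as AWP risks. The size is δ/π: 1.0 to 1.7 CACE points per 0.5 point of non-drug effect. This rests on an assumed δ and assumed falls in rocuronium use of 50 to 30 points. Whether any such effect will occur is unknown.

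Second, the step-specific CACE cannot carry a site effect. This follows from the design, not from a statement in the article. The shift is up to about 2.1 points before division by π, against a planned 2.7, if one site is at 7.4% and the other four at an assumed 3.3%. It depends on the realised order and is small if between-site variation is as low as the protocol's ICC implies.

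**What to change.** 1. Name the planned two-stage residual inclusion model, with site and period effects, as the main CACE analysis. Label the step-specific estimates supportive or descriptive.
2. Fit the same site-and-period model to the sedation and analgesia data already collected: any agent given, time to first dose, and depth.
3. Replace the unqualified validity sentence with one saying that the CACE also assumes phase affects AWP only through blocker choice, and that the education package may breach this.
4. If sedation changes with phase, report that the CACE cannot be attributed to blocker choice alone. Add a sensitivity range over an assumed non-drug effect δ, using (phase effect − δ)/π. State that a sedation change may itself follow from the agent, so the range is not a correction and the observed sedation effect should not simply be subtracted.

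The cost is a few extra models on existing data, some changed wording, and a more guarded CACE claim. No new data collection or change to the primary analysis is needed.

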However, similar to AWP, there is a significant knowledge gap with respect to critically ill, mechanically ventilated ED patients. Prior ED-based PTSD work has largely focused on traumatic injury or specifically excluded mechanically ventilated patients [34–37]. In a cohort study of 99 ED patients, our team demonstrated clinically significant PTSD symptoms in 31% of patients with acute respiratory failure, but only 9 patients (9.1%) were mechanically ventilated [38]. Therefore, the burden of PTSD in this cohort is unknown, and the ED could be an optimal target for improving mental health outcomes for several reasons. Critical illness-related mental health disorders are linked to exposures during care, and early frightful memories during illness are linked to higher PTSD prevalence [1, 26]. In addition, delays in care for PTSD are common and linked to refractory symptoms [6, 39–41]. This evidence suggests the early period of critical illness opens a window to reduce psychological morbidity in survivors. The ED-AWARNESS-2 Trial will inform creation of interventions to be used during (not after) an event to mitigate symptom development, and it will use the ED as a target in which to improve outcomes during the “golden hours” (Fig. 2) [34, 42].

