**Fig. 2 Fig2:**

Example novel paradigm and hypothesized causal pathway for improving patient-centered outcomes. It is possible that by addressing the early period of critical illness in the emergency department, modifiable targets (increasing provider compassion, decreased patient-perceived threat, preventing awareness with paralysis) can be used to improve patient-centered clinical outcomes

There is significant rationale to target rocuronium use in the ED as a means to prevent AWP. In the ED-AWARENESS Study and ED-SED Pilot Trial, 19/23 (92.6%) AWP patients received rocuronium [19, 23]. In multivariable analysis, rocuronium was independently associated with AWP (adjusted odds ratio, 6.05; 95% CI, 1.46–17.56) [19, 23]. Importantly, AWP was not associated with other sedation-related variables, including (1) sedation monitoring; (2) analgesics, sedatives; or (3) sedation depth. This confirms that a proposal to target ED-based rocuronium may have the greatest chance to improve safety and prevent AWP. This is critical as data from the National Emergency Airway Registry (*n* = 17,583) show rocuronium use was 5% for intubations in 2002, yet up to ~ 45% by 2012 [14]. Use was up to 49% in our ED SED Study, and 60% in the ED-SED Pilot Trial [17, 21]. This indicates that AWP is likely a growing health problem. Contrary to a 5-min duration of succinylcholine (the historical default NMB), rocuronium can paralyze for up to 150 min, greatly increasing AWP risk. In addition, in clinical trials comparing rocuronium versus succinylcholine, with respect to intubating conditions, data has either favored succinylcholine or shown no difference in outcomes [43–45]. However, other preliminary work from our research team did not show an association between rocuronium and AWP risk, but rather pre-intubation mental status [24]. This suggests equipoise in the data and further confirms the need for this large-scale clinical trial.

Our objective is to conduct a pragmatic clinical trial aimed at limiting rocuronium exposure in order to reduce the proportion of mechanically ventilated ED patients experiencing AWP. We hypothesize that limiting rocuronium exposure in the ED, using succinylcholine as the default NMB of choice, will significantly reduce the proportion of patients experiencing AWP.

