### Sample size justification

Our sample size is designed to detect a difference in the proportion of patients experiencing AWP in the control versus the intervention phase. The sample size must be inflated by estimating the design effect, to account for the intraclass correlation coefficient (ICC). More common outcomes are associated with higher design effects, whereas lower prevalence outcomes, such as AWP, have smaller ICCs [94]. Based on our data, and extensive supporting analyses from more than 100 ICC values obtained from research studies and population health outcomes analyses (*n* > 1,000,000 patients) which show a strong linear association between the ICC and outcome prevalence in clustered binary data, we conservatively estimate an ICC of 0.001 [94]. From our preliminary multicenter data, due to a reduction in rocuronium use, it is reasonable to estimate a reduction in the proportion of patients experiencing AWP from 4.0% in the control phase to 0.2% in the intervention phase (data from the operating room), which would require a total sample size of 1650 patients [95]. To err on the side of conservative assumptions, and to account for possible non-adherence during the study, we will assume a prevalence of AWP of 3.3% in the control phase and 0.6% in the intervention phase. These conservative estimates are based on our prior work (control phase), and the intervention phase event rate is similar to that seen in operating room patients managed with total intravenous anesthesia and when longer-acting NMB is limited [10, 19, 96]. Thus, these calculations are both clinically important (would prevent ~ 10,000 AWP cases annually in the USA) and plausible from supporting preliminary work. Considering there are 5 sites and 6 time periods, for 80% power with *α* of 0.05, we will need a total sample size 3090 patients.

With respect to PTSD, if we estimate that PTSD occurs in 45% of those with AWP [5, 6, 9] and 20% of the rest of the cohort [25–27], assuming *α* = 0.05 and power = 0.80, using two-sided *Z*-test with pooled variance, a sample size of 1192 patients will be required for the multivariable model above. With respect to perceived threat, even if correlation between perceived threat and PTSD symptoms is smaller than our prior work (0.3) then a minimum of 412 patients is estimated to detect the mediated effect of perceived threat between clinician compassion and PTSD symptoms [38, 97, 98].

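### The model linking AWP to later PTSD symptoms leaves pre-intubation mental status off its fixed covariate list, although the team's own cohort tied it to AWP and the trial collects it

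*Protocol article*

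**What the plan says.** Under Proposed statistical methods, the protocol article plans a multivariable logistic regression of 30-day PTSD symptoms on AWP, the main exposure, with covariates chosen in advance. The rule for choosing them is "The model will be adjusted for covariates previously associated with PTSD symptoms in critical illness survivors". The numbered list starts with age, sex and prior psychological trauma or mental health history, and ends with "4) illness severity; and (5) receipt and dose of benzodiazepines". Two further terms follow: "We will adjust for race, given known racial disparities in PTSD symptoms", and "In all of these models, cluster effect will be modeled as a fixed effect, using cluster indicator in the model". Similar analyses are promised for the other secondary outcomes.

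Two other places bear on this list. In the Background, after Fig. 2, the authors say that other preliminary work by their team "did not show an association between rocuronium and AWP risk, but rather pre-intubation mental status". The reference given there is the one cited for the single-center cohort with 66 AWP events in 886 patients, the largest of the three cohorts described and from an enrolling site. The Data section states: "Pre-intubation mental status, drugs used to facilitate intubation, and ventilator settings in the ED will be collected".

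**The concern.** AWP is not randomised in this model, so its coefficient can be read as independent of other factors only if the common causes of AWP and PTSD symptoms are adjusted for. The article itself names pre-intubation mental status as a correlate of AWP. A route to PTSD that bypasses AWP is plausible: a patient who is alert before intubation may keep other distressing memories of the ED, and the Background notes that "early frightful memories during illness are linked to higher PTSD prevalence". No listed covariate measures alertness. Illness severity may be a partial stand-in, but the article does not define the severity measure.

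At stake is the estimate of how much AWP adds to PTSD symptoms, and the parallel estimates for depression, anxiety and quality of life. The primary comparison of AWP between phases is not affected.

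**Working it through.** **1. The plan's own figure.** Sample size justification gives 1192 patients for this model, from 45% versus 20% PTSD, two-sided α 0.05, power 0.80 and pooled variance. The AWP prevalence used is not stated; I infer 2.0%. With 49 patients without AWP per patient with AWP, the pooled proportion is 0.98×0.20 + 0.02×0.45 = 0.205. The number without AWP is

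[1.960·√(0.205×0.795×50) + 0.8416·√(0.20×0.80 + 0.45×0.55×49)]² / 0.25² = (5.595 + 2.950)² / 0.0625 = 1168.3.

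The total is 1168.3/0.98 = 1192, so the figure reproduces. At 1.95%, the mean of the two rates in "we will assume a prevalence of AWP of 3.3% in the control phase and 0.6% in the intervention phase", the total is 1222. With the 40% response rate in the Discussion, 0.40×3090 = 1236 responders are expected, about 24 of them with AWP (1236×0.0195). The size of the model is not in question.

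**2. Assumptions for the illustration (not in the article).** Half of patients are alert before intubation. AWP is R = 2 to 6 times as frequent in them. Alertness multiplies the odds of PTSD by m = 0.5 to 2. Patients who are not alert have the article's rates, 20% without AWP and 45% with it, so the true odds ratio is (0.45/0.55)/(0.20/0.80) = 3.27.

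**3. Formula.** The alert share is R/(1+R) among AWP patients and close to 50% among the rest. Average the PTSD risks over these shares and take the odds ratio.

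- m = 2: alert patients have 33.3% PTSD without AWP and 62.1% with it. Overall risk without AWP is 26.7% (odds 0.364).
- m = 0.5: the corresponding risks are 11.1% and 29.0%. Overall risk without AWP is 15.6% (odds 0.184).

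| R | m | PTSD risk with AWP | OR by hand | OR from fitted model |
|---|---|---|---|---|
| 6 | 2 | 0.857×62.1 + 0.143×45 = 59.6% | 4.06 | 4.08 |
| 2 | 2 | 0.667×62.1 + 0.333×45 = 56.4% | 3.55 | 3.56 |
| 2 or 6 | 1 | 45% | 3.27 | 3.27 |
| 2 | 0.5 | 0.667×29.0 + 0.333×45 = 34.4% | 2.84 | 2.83 |
| 6 | 0.5 | 0.857×29.0 + 0.143×45 = 31.3% | 2.47 | 2.46 |

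The last column comes from logistic models with site effects, fitted to expected counts in a design of 5 sites and 6 periods with 1236 patients. Adding mental status returns 3.27 in every row.

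**4. Size against precision.** The standard error of the log odds ratio is about 0.42 to 0.45. The largest shifts are ln(4.08/3.27) = 0.22 and ln(2.46/3.27) = −0.28, roughly half to two-thirds of a standard error.

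**5. Price of adjusting.** With R = 6, the standard error rises from 0.421 to 0.426 (1.1%) for m = 2 and from 0.447 to 0.457 (2.1%) for m = 0.5. Adding period as well takes the latter to 0.458 (2.5%).

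**6. Phase and period.** Over 15 control and 15 intervention site-periods, 3.3/(3.3 + 0.6) = 85% of AWP cases would fall in the control phase. If phase and time affect PTSD only through AWP, leaving them out changes nothing: the odds ratio is 3.27 either way, with a standard error of 0.416 without them and 0.419 with them. If PTSD drifts over the trial with an odds ratio of 0.5 to 2.0 from first to last period (assumed), omission gives 3.61 down to 2.88. If phase acts directly on PTSD with an odds ratio of 0.67 to 1.5 (assumed), omission gives 3.62 down to 2.90.

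**The case against.** The strongest reply is that no passage links mental status, phase or calendar time to PTSD except through AWP, and without such a link there is no confounding. That stands. The sentence on frightful memories does not say that alert patients have more of them apart from AWP, which is itself such a memory. A reader might infer that the planned estimate is biased upward. The article does not support this: the bias may be zero, upward or downward.

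A reader might also infer that the list ignores everything that determines AWP. It does not. Site is included, and AWP was 3.3% and 7.4% in the two single-center cohorts. Benzodiazepine dose bears on under-dosing, which the Background names as an operating-room risk factor, although the team's ED data found no association with sedatives.

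Nor is it an error to choose covariates for their association with the outcome; that is an accepted way to control confounding, and a factor that affects only the exposure is not a confounder. For the same reason, mandatory adjustment for trial phase does not follow. Phase acts much like an instrument for AWP, so adjusting for it may remove no bias and can amplify bias from unmeasured confounders.

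Finally, this is a secondary observational analysis, and an analysis plan that is not shown may add sensitivity models. That lowers the weight of the point. It does not remove it, because the article gives an explicit list and leaves out a collected variable that the authors themselves tie to AWP.

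**Conclusion.** The point holds as a specific gap in the covariate list. Pre-intubation mental status is a credible candidate confounder: its association with AWP comes from the team's own 886-patient cohort, it is a baseline variable, and it will be recorded. Whether it confounds depends on an effect on PTSD outside AWP that the article neither quantifies nor signs. Under the assumed ranges, the model would return an odds ratio of about 2.5 to 4.1 instead of 3.27, and exactly 3.27 if there is no such effect. These values are illustrative. They hold site fixed but not the other planned covariates, so any overlap of mental status with illness severity or sedation would shrink the shift.

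Calendar period is a reasonable companion, since the same section adjusts for time in the primary and instrumental-variable analyses. It matters only if PTSD symptoms have a secular trend, and none is documented.

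**What to change.** In Proposed statistical methods, add pre-intubation mental status to the a priori covariates of the model of AWP and PTSD symptoms and of the matching HADS and EQ-5D models. Add calendar period as a covariate or a named sensitivity analysis. Use trial phase in a sensitivity analysis only. Give the reason for the addition: mental status is a possible common cause of AWP and the outcome.

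This takes a line or two of text and no new data collection. The standard error of the AWP log odds ratio rises by about 1–3%.
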